### Volunteers

We invite volunteers in the project to fill out two questionnaires: the first one immediately after the training session and the second one around 4 months after training. The first questionnaire assesses satisfaction with the training session. The second questionnaire includes questions on gender, age, family status, education, employment, motivation for becoming a volunteer, collaboration with the project coordinators, collaboration with other organizations, the collaboration between the volunteers, and characteristics of the family club such as location, number of sessions, and activities. The volunteers also fill out a web-based questionnaire after each session providing information on the date, the number of participants, which value poster and activities are used, what the meal was, and if any guests participated.

### Statistical analysis

We analyze the primary and secondary outcomes at post-intervention (T2) and follow-up (T3). We use linear regression for normally distributed outcomes and apply robust standard errors to correct for the correlation between observations participating in the same FCD group. In the case of heavily skewed data, we use non-parametric rank-based tests. To check whether the first-come-first-served principle or the allocation of vulnerable families conducted by the volunteers introduce imbalances in the allocation to FCD and the waitlist control, we test for statistical differences in observable characteristics of the two groups using t-tests. In the analysis of the effectiveness of FCD, the hypothesis tested for each outcome is that the FCD group will score better than the wait-list control group. We test this hypothesis with a binary variable indicating the intervention group. We include variables measured at baseline with indications of imbalances (*p* < 0.1) as control variables and apply two-sided tests with 0.05 significance levels throughout. As all outcomes represent a different aspect of the expected outcome of the intervention we do not consider multiple testing issues. We analyze primary and secondary endpoints according to an intention-to-treat (ITT) principle and handle missing data with multiple imputations. Parametric imputation models are preferred, but in case of severe non-normality or convergence issues, we use predictive mean matching or other non-parametric options. We include the 12-month outcome data for exploratory analyses but can also be used as tools in secondary analyses of missingness. Exploratory analysis of data from all three measurements (T1 - baseline, T2 - 6 months and T3–12 months) will be carried out using mixed-effect regression and possibly latent growth curve analysis. The purpose is to assess the longer-term effects of the intervention and to understand how the psychosocial characteristics of the families involved develop over time. In addition to the primary analysis, we will perform subgroup analyses to examine potential differences between subsets of participants. Hence, we analyze subgroups according to the following characteristics: vulnerability (vulnerable or non-vulnerable families); family composition (single parents or cohabiting parents); the age of target child (< 8 years old or ≥ 8 years old); partner organization (KFUMs Sociale Arbejde, FDF, or KFUM Spejderne); the number of volunteers in the FCD; and the number of sessions attended (dose).

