### Intervention and training

The FCD concept was developed by the project partners in the developmental part of the project in 2017. The principles are described in a concept book and a practical guide. Theoretically, FCD is based on social learning theory, neuroscience, and positive psychology. The focus is on proving positive experiences for families and building relationships. Volunteers should meet the families with a positive attitude and show them that they each are important contributors to the family club. The materials also recommend that volunteers use praise and apply predictability and routines in the family club. The volunteers should create a program for each session and present it to the families. The program should include the following elements: welcome, activity, dinner, goodbye.

A family club is run by a volunteer team comprised of a leader and two-to-five further volunteers. Each club consists of up to nine families who meet every second week for 6 months (12 sessions). The club runs for 6 months at a time to ensure enough time for relationships to grow and to create a predictable structure around the club. In the first months, the focus is getting to know each other whereas there is more focus on building both the internal and external networks in the last part of the intervention. The aim is that an FCD will run for consecutive periods but families and volunteers sign up for 6 months at a time. If participants wish to stay in the FCD for another 6 months after finishing the first 6 months they can. Although each club includes both vulnerable and non-vulnerable families all families must participate on equal grounds.

The FCD is based on the following four principles: (1) Meal community; (2) Play, learning, and togetherness; (3) Support and advice; and (4) Bridging to the civil society and the public sector. Each meeting in the FCD must include the first two principles, i.e. meal and play. The 12 sessions center around seven value posters that can be put on the wall in the room. The seven values are: (1) Fun with smiles; (2) Together but not in line; (3) The time is now; (4) Notice and say thank you; (5) More than me; (6) Courage to dare; and (7) Taste the world. The seven values are explained in the FCD concept book and activities are linked to the seven values.

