### Wait-list control group

Families who are on the wait-list will be offered participation in FCD after approximately 6 months. We do not expect all wait-list families to participate in FCD in the second period. Some areas will still not offer an FCD at this time and we also expect that some families may not be interested in participating at this time point. Therefore, we will have both families who receive FCD in the second period and families who never receive FCD in the control group. Families in the wait-list control may participate in other volunteer projects.

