### Outcomes

Data are collected through web surveys at three time-points: baseline, post-intervention (6 months after baseline), and follow-up (12 months after baseline). Participants receive an e-mail with a direct link to the questionnaire. Reminders are sent by text message and e-mail. If the families need help to fill out the questionnaire a student will call them. Families receive a small gift at each of the three data collections. At baseline, they receive a cookbook for children, at post-intervention, they receive a 150 DKK (~ 20 EUR) electronic gift card, and at follow-up, they receive a 100 DKK (~ 15 EUR) electronic gift card. When signing up the families are informed that they will receive a small gift after completing each questionnaire. Data are collected in a secured online survey database. The trial statistician and the principal investigator will have access to the full dataset.

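### The 12-month group contrast is given two conflicting statuses and, because controls are offered FCD at about 6 months, does not estimate the longer-term effect of FCD versus no FCD

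*Protocol article*

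**What the plan says.** Surveys are taken at "baseline, post-intervention (6 months after baseline), and follow-up (12 months after baseline") (Outcomes). The Statistical analysis section opens with "We analyze the primary and secondary outcomes at post-intervention (T2) and follow-up (T3"). For each outcome, "We test this hypothesis with a binary variable indicating the intervention group", with two-sided tests at 0.05 throughout, and "We analyze primary and secondary endpoints according to an intention-to-treat (ITT) principle". On multiplicity it states that "we do not consider multiple testing issues", because each outcome captures a different aspect of the expected effect.

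Further down, the same section says "We include the 12-month outcome data for exploratory analyses". It describes the mixed-effect and growth-curve models over the three waves as exploratory and as meant to assess longer-term effects.

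Three other statements bear on what the groups are by 12 months:

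- Methods and design, and Wait-list control group: wait-list families are offered FCD after about 6 months, where a club exists in their area.
- Wait-list control group: not all are expected to take part, so "we will have both families who receive FCD in the second period and families who never receive FCD in the control group".
- Intervention and training: "If participants wish to stay in the FCD for another 6 months after finishing the first 6 months they can".

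The Primary outcome section names SWEMWBS but no time point. Power considerations refers to a baseline to post-intervention correlation and says nothing about 12 months.

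**The concern.** Two things are wrong.

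First, the status of T3 is not settled. One sentence analyses the primary outcome at T2 and T3 without ranking them. A later one makes the 12-month data exploratory. A reader of the final report could not tell from this text whether SWEMWBS at 12 months is a primary or an exploratory result. The reason given for ignoring multiplicity, that the outcomes differ, does not cover testing the same outcome twice.

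Second, the T3 contrast does not answer the question set for it. By 12 months some controls will have had FCD in the second period and others none, depending on local clubs and on interest. Some FCD families will have had a second period. An intention-to-treat comparison then estimates the effect of an immediate versus a delayed or absent offer. Nothing in the section says so.

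Two misreadings are at stake: a sustained benefit reported as fade-out because controls have caught up, and success claimed from whichever time point turned out positive.

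**Working it through.** **Inputs from the article (Power considerations, Statistical analysis).** 80 control and 120 FCD families; standardised effect 0.35; baseline to post-intervention correlation r = 0.50; two-sided 0.05; stated power about 80%.

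**Step 1: reproduce the stated power.** With adjustment for baseline, the residual SD is √(1 − 0.50²) = 0.866. The standard error of the group difference is 0.866 × √(1/80 + 1/120) = 0.866 × 0.1443 = 0.125. The noncentrality is 0.35 / 0.125 = 2.80. Power is 79.6% by noncentral t (197 df) and 80.0% by the normal approximation. The stated figure reproduces, and it concerns the post-intervention comparison.

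**Step 2: the T3 contrast under control uptake.** Let q be the share of controls who receive FCD before T3. The article gives no value, so q is an assumption and a range is shown. Assume also that FCD families keep the full 0.35 SD, that crossed-over controls gain the same 0.35 SD, that r = 0.50 also holds at T3, and that nobody drops out. Then

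T3 contrast = 0.35 − 0.35q = 0.35(1 − q), with noncentrality 0.35(1 − q) / 0.125.

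| q (assumed) | T3 contrast (SD) | Noncentrality | Power |
|---|---|---|---|
| 0 | 0.350 | 2.80 | 80% |
| 0.10 | 0.315 | 2.52 | 71% |
| 0.25 | 0.263 | 2.10 | 55% |
| 0.40 | 0.210 | 1.68 | 39% |
| 0.50 | 0.175 | 1.40 | 29% |
| 0.60 | 0.140 | 1.12 | 20% |
| 0.75 | 0.088 | 0.70 | 11% |

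Under this model the contrast reaches zero only at q = 1. In every row the true effect on FCD families is a fully sustained 0.35 SD.

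**Step 3: crossover and real decay look alike.** Suppose instead that FCD families keep half the effect at T3 (again an assumption). The contrast is 0.175 − 0.35q: 0.088 at q = 0.25, zero at q = 0.50 and −0.088 at q = 0.75. A contrast of 0.088 thus arises from full retention with 75% uptake or from half retention with 25% uptake. The T3 difference alone cannot tell these apart.

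**Step 4: one outcome, two tests.** Assume the T2 and T3 test statistics correlate 0.5. The article gives no such figure; its 0.50 is baseline to post-intervention. With no true effect, two two-sided tests at 0.05 give a 9.1% chance of at least one rejection in either direction (9.5% at correlation 0.3, 8.3% at 0.7). The chance of at least one false result favouring FCD is 4.5%, against 2.5% for a single test.

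**The case against.** The strongest reply is that the later sentence already qualifies the opening one. The opening lists time points and ranks none, the 12-month data are then called exploratory, and the power case rests on the post-intervention comparison, which points to T2. An exploratory analysis may properly look at longer-term effects, and the Discussion calls causal conclusions tentative. This reading is reasonable and is probably what was meant. But nowhere is T2 named as the single primary time point, and the opening sentence covers the primary outcome at both times. Nor does the exploratory label say what the T3 contrast estimates.

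A reader might go further and infer that T3 can show nothing about longer-term effects. The article does not support that. It expects incomplete uptake: some areas will still have no club, some families will not be interested, and most controls are expected to come from areas with no club yet (Allocation). Low uptake is therefore plausible, and at q = 0.10 the contrast keeps 90% of the assumed effect. A positive T3 difference would still be informative.

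A reader might also take 9.1% as the chance of a false claim of benefit. It counts rejections in both directions; the figure for benefit is 4.5%.

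Finally, adjusting secondary outcomes for multiplicity is a separate matter on which the article has made an open choice. It does not follow from this point.

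**Conclusion.** The point stands in limited form. The section gives T3 two statuses, and its planned T3 contrast estimates immediate versus delayed or absent offer, not FCD versus no FCD over the longer term. A null T3 result could not be read as fade-out. How far the contrast shrinks depends on a control uptake that the article does not give: from 71% power at 10% uptake to 11% at 75%, if the effect is fully sustained and equal in crossed-over controls. The error from testing SWEMWBS at both times is moderate and rests on an assumed correlation. This point leaves the T2 analysis and the stated 80% power untouched.

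**What to change.** In Statistical analysis:

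1. Name SWEMWBS at T2 as the single primary test.
2. Reword the opening sentence so that primary and secondary outcomes are analysed at T2, and T3 is exploratory for all outcomes.
3. State that the T3 group contrast estimates immediate versus delayed or absent offer.
4. Report beside it the share of controls who took up FCD and the share of FCD families who continued.
5. Make no claim of sustained effect or of fade-out from that contrast.

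Change within the FCD arm may be shown as description, but it should not replace the T3 group contrast: it has no comparator and is itself affected by families who continue. A comparison restricted to never-treated controls would not be intention-to-treat and would be open to selection by area and interest.

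The cost is a few sentences and two reported percentages. The downside is that no confirmatory 12-month claim can be made.

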#### Secondary outcomes

The secondary outcomes include the following measures. It was important to both covers a relatively broad area of outcomes that we believe potentially can be impacted by the intervention but also keep the questionnaire relatively short. Therefore, we have shortened some of the included measures.

**Parent Behavior Inventory (PBI)** is a 20-item measure of parenting behavior of parents of early school-aged children. The PBI includes two subscales with high internal consistency: Supportive/engaged (α = .83) and hostile/coercive (α = .81). The PBI has adequate test-retest reliability (r = .69–.74) in an ethnically diverse sample of mothers. To reduce the total number of items we include 10 items – 5 from each of the two subscales; items 6, 10, 11, 12, 14 for Supportive/Engaged, and items 5, 9, 15, 17, 20 for Hostile/Coercive. The score range is 0–25 for each subscale. A high score is better for Supportive/Engaged, a low score is better for Hostile/Coercive [52]. Cronbach’s alpha is 0.66 for the supportive/engaged subscale and 0.55 for the hostile/coercive subscale in a subsample of the included families.

**The Parenting Stress Scale (PSS)** is an 18-item measure of parenting stress that is rated on a five-point scale (Strongly disagree, Disagree, Undecided, Agree, Strongly Agree). We use the revised Danish version with 16 items where the original items 2 and 11 are left out. The Danish version consists of two subscales: Parental Stress (9 items) and Lack of Parental Satisfaction (7 items). Responses are reversed for the lack of parental satisfaction items and all responses for all items are dichotomized (0–1) before scoring. Total score range 0–9 (Parental Stress subscale) and 0–7 (Lack of Parental Stress subscale). A low score is better for both subscales [53]. Cronbach’s alpha is 0.76 for the parental stress subscale and 0.82 for the lack of parental stress scale in a subsample of the included families.

**The general self-efficacy scale (GSE)** is a 10-item measure of optimistic self-beliefs to cope with a variety of difficult demands in life. To reduce the total number of items we include 3 items (8, 9, and 10). The score range is 3–12 and a high score is better. Cronbach’s alpha for the 3-item version is 0.87 in a subsample of the included families.

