### Power considerations

We carried out a power analysis in the design phase to assess the statistical power for testing the main hypothesis. As this study is among the first effectiveness studies of a volunteer intervention there is a lack of previous research to guide the power analysis. Two reviews examine the effect of home visiting interventions (including both professional and paraprofessional providers). Nievar et al. found an average effect size of 0.37 [0.21:0.53] on maternal behavior across 60 studies of home-visiting for at-risk families [56]. The average effect size did not differ significantly between studies with professional and paraprofessional home visitors. Filene et al. found an average effect size of 0.23 [0.13:0.33] on parent behaviors and skills [49]. Two randomized studies examine the effects of volunteer parent training programs for parents with children with ADHD or behavior problems. Chacko & Scavenius report effect sizes post-intervention of 0.3 for parental stress, 0.46 for parenting behavior, and 0.65 for parenting competence [40]. Gardner et al. report effect sizes post-intervention of 0.40 for parenting confidence and 0.65 for parenting skills. None of these studies, however, report results on parental well-being.

We expect controls to constitute approximately 80 out of 200 families. For normally distributed outcomes, a sample of 200 participants (80 control and 120 intervention) would yield a statistical power of approx. 80% with a type 1 error rate of 0.05 for an effect size of 0.35 standardized mean difference (SMD) and a correlation between baseline and post-intervention measures of 0.50.

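### The fallback to rank-based tests for heavily skewed outcomes names no version that keeps the control variables or the club clustering this non-randomised comparison needs

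*Protocol article*

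**What the plan says.** All of the following are in the protocol article.

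- **Main method (Statistical analysis).** "We use linear regression for normally distributed outcomes and apply robust standard errors to correct for the correlation between observations participating in the same FCD". The club correction is stated here only, and it is attached to linear regression.
- **Fallback (next sentence).** "In the case of heavily skewed data, we use non-parametric rank-based tests". The test is not named, and no threshold for heavy skew is given.
- **Scope (same section).** "the hypothesis tested for each outcome is that the FCD group will score better than the wait-list control group", followed by "We test this hypothesis with a binary variable indicating the intervention group". Baseline variables that show imbalance at p < 0.1 are to enter "as control variables and apply two-sided tests with 0.05 significance levels throughout". Primary and secondary endpoints are analysed by intention to treat with multiple imputation, and predictive mean matching is allowed for severe non-normality.
- **Allocation.** Coordinators steer on vulnerability and on Danish language skills. The authors regard the result as equivalent to random only given those two characteristics.
- **Discussion.** Comparability of the groups cannot be guaranteed, and causal conclusions will be tentative.
- **Secondary outcomes.** For the Parenting Stress Scale, "all responses for all items are dichotomized" before summing, which gives scores of 0–9 and 0–7 with low scores better.

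**The concern.** The comparison rests on two devices: control variables, because families are not randomised, and robust standard errors, because intervention families share clubs. A rank test in its usual two-sample form has room for neither. It compares the two sets of ranks as if the families were independent and exchangeable between groups.

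For a heavily skewed outcome, the section therefore points two ways. One sentence prescribes a test with no covariates. The sentences after it prescribe a group indicator with control variables for each outcome. An analyst who follows the first would report some secondary outcomes unadjusted, next to adjusted results for the others. The false-positive rate would be above the nominal 5%, and there would be no effect estimate on the scale used elsewhere. Because heavy skew is undefined, the choice of route would be made after seeing the data.

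**Working it through.** **Inputs from the article.** 80 control and 120 intervention families, SMD 0.35, baseline-to-post correlation r = 0.50 (Power considerations); about nine families per club (Allocation); two-sided 0.05 and adjustment when p < 0.1 (Statistical analysis).

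**Assumptions.** The article gives neither the club ICC nor the size of any baseline imbalance. Both are varied below. Controls are taken as independent.

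**1. The plan's own figure.** In SD units, the standard error of a difference between groups is s = √(1/80 + 1/120) = 0.1443. With adjustment for the baseline score, the residual SD is √(1 − 0.5²) = 0.866. Power = Φ(0.35/(0.866 × 0.1443) − 1.96) = Φ(2.80 − 1.96) = 79.96%. This reproduces the stated 80%, so 80/120 and r = 0.5 are a coherent base for what follows.

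**2. Unadjusted baseline imbalance, no true effect.** The difference in a baseline score that just meets the plan's p < 0.1 trigger is 1.645 × 0.1443 = 0.24 SD. Left unadjusted, it biases the outcome by 0.5 × 0.24 = 0.12 SD, or 0.12/0.1443 = 0.83 standard errors.

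Type I error of an unadjusted t-type test = Φ(−1.96 + 0.83) + Φ(−1.96 − 0.83) = 13.2%. For a rank-sum test on normal data (relative efficiency 0.955), the shift is 0.83 × √0.955 = 0.81, which gives 12.8%. By the t-type formula, an imbalance of 0.2 SD gives 10.7% and 0.3 SD gives 18.0%.

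**3. Ignored club clustering, no true effect.** Only the intervention arm is clustered, with design effect 1 + (9 − 1) × ICC. The true variance is 1/80 + DE/120, while the test assumes 1/80 + 1/120 = 0.02083.

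| ICC | DE | True variance | 1.96 × √(0.02083/true variance) | Type I error |
|---|---|---|---|---|
| 0.01 | 1.08 | 0.02150 | 1.929 | 5.4% |
| 0.05 | 1.40 | 0.02417 | 1.820 | 6.9% |
| 0.10 | 1.80 | 0.02750 | 1.706 | 8.8% |
| 0.20 | 2.60 | 0.03417 | 1.531 | 12.6% |

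**4. Simulation check.** 2,000 null trials per setting. Mann-Whitney is compared with linear regression that always adjusts for the baseline score and uses cluster-robust errors. The skewed outcome is one assumed floor-heavy 0–7 score.

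| Setting | Rank test, skewed / normal | Adjusted cluster-robust regression, skewed / normal |
|---|---|---|
| No imbalance, ICC 0 | 6.1% / 4.8% | 6.2% / 5.5% |
| Imbalance 0.23 SD, ICC 0 | 12.7% / 11.6% | 5.2% / 4.7% |
| No imbalance, ICC 0.05 | 6.4% / 6.5% | 6.0% / 5.4% |
| No imbalance, ICC 0.10 | 7.4% / 6.4% | 6.1% / 5.1% |
| Imbalance 0.23 SD, ICC 0.05 | 12.7% / 13.3% | 5.8% / 5.5% |

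The Monte Carlo standard error is about 0.5 points near 5% (√(0.05 × 0.95/2,000)) and 0.7 points near 12%.

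In these runs the ICC applies to the residual part of the outcome, which is 75% of the variance. A nominal 0.10 is therefore 0.075 of the total, for which the formula in step 3 gives DE 1.6 and 7.8%. This explains much of the gap from 8.8%.

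Further simulations gave rank-test type I errors of 12.5% (normal) and 10.5% (floor-heavy) at 0.24 SD imbalance. For clustering alone, 5,000-trial runs gave 6.2–6.4% at ICC 0.05 and 8.0–8.9% at 0.10. Another check put clustering at about 7–10% over that ICC range. Taken together, the results are about 10–13% for imbalance and about 6–10% for clustering.

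**5. Imputation.** Rubin's rules pool an estimate and its variance over the imputed data sets. A rank test returns a statistic and a p-value, so the planned imputation can be run but has no standard quantity to pool.

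**The case against.** The strongest reply is that the article never says adjustment is dropped. It does not name Mann-Whitney, and the sentences on the group indicator and control variables are not limited to linear regression. Covariate-adjusted and clustered rank methods exist, proportional-odds regression generalises the Wilcoxon test, and a full analysis plan could name one. This is fair: the loss of adjustment and clustering is inferred from an unqualified reference to tests. It does not settle the matter, because the club correction is tied in words to linear regression, and the ordinary meaning of the fallback conflicts with the sentences after it.

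Several stronger readings are tempting, but the article does not support them.

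- **That the fallback costs about 12 points of power** (80% falls to 68% without the baseline score). The linear branch itself adds the baseline score only if it is imbalanced at p < 0.1, so this gap is not specific to the rank branch. The article also limits its power figure to normally distributed outcomes.
- **That type I error reaches 7.7–14.5%.** Those values need control families clustered within 8 or 16 areas, numbers found nowhere in the article. The planned robust errors, which cover shared clubs, would not correct such clustering either.
- **That imputation is abandoned.** It is planned for all primary and secondary endpoints, with an option for non-normal data. Only the pooling is unresolved.
- **That the branch will certainly be used, or will reach the primary outcome.** No distributions are reported. Dichotomised items make skew plausible for the stress subscales but do not establish it, and nothing shows whether SWEMWBS is affected.

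The clustering part is also modest. With nothing wrong at all, both methods rejected in about 6% of the skewed trials, so excesses of a point or so should not be over-read.

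**Conclusion.** The point holds for any outcome judged heavily skewed. As written, the fallback prescribes a class of test that in standard form omits both the conditioning on which the authors rest comparability and the clustering they correct for elsewhere.

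Lost adjustment is the larger harm: type I error of about 10–13% at an imbalance of about 0.24 SD. Ignored clustering gives about 6–10% at ICC 0.05–0.10. The comparator is about 5–6%, for a regression that always adjusts for the imbalanced variable. The plan's linear branch would adjust for it only when its p < 0.1 trigger is met.

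These sizes rest on assumed values for the imbalance, the ICC and the shape of the skewed score, on r = 0.5 from the article, and on independent controls. How many outcomes are affected is unknown. The text should be changed, but the point does not show that the primary analysis is wrong.

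**What to change.** Replace the fallback sentence. For skewed or bounded outcomes:

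- Keep the same regression with the group indicator and the same control variables, always including vulnerability status and Danish language skills, with cluster-robust or cluster-bootstrap intervals.
- Where a scale is too coarse for that, use proportional-odds regression with the same covariates and clustering.
- Pool the group effect over the imputations by Rubin's rules.
- Keep rank tests only as a labelled sensitivity analysis.

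If an adjusted, cluster-aware rank method was intended all along, name it and say how its results are combined over imputations.

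The cost is a few sentences of analysis-plan wording and slightly more analysis work in standard software. No further data are needed.
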